### Outcomes

The primary outcome of this study is the change in emotion regulation ability, measured by the raw score of the FEEL-KJ (74). Here, we expect an increase in emotion regulation after the intervention of the experimental group in total (as well as for each clinical experimental subgroup) compared to the control group in total (as well as for each clinical control subgroup).

As exploratory outcomes, we will investigate if the application of tDCS improves the disorder-related clinical symptomatology, quality of life or emotion regulation, whereas changes in raw scores of the related self- and parental reports (as summarized in Psychological Self- and Parental Ratings) are defined as secondary endpoints.

Further we will explore if indices of emotion recognition [measured via Frankfurter Test and Training for Recognizing Facial Affect (FEFA II) and the Emotion Recognition Task (ERT)], and (implicit) emotion regulation (measured via eSTROOP) improve from before to after tDCS stimulation. In addition, measures of attentional bias [*via* Attentional Bias Task (ABT)] and working memory (*via* e n-BACK) will give insight regarding potential improvements in the related indices from before to after tDCS stimulation. Indices of each task (such as the number of correct behavioral assignments, commission, omission, reaction times, eye gaze fixation duration, pupil dilation, brain activation, brain connectivity) are summarized in Eye Tracking and Behavioral Measures and fMRI Procedure and Measures.

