In line with the framework of the Research Domain Criteria project (RDoC of the United States' National Institute of Mental Health), which orients psychiatric research to uncover the neural systems underlying psychopathology and the behavioral components that flow across diagnostic categories (59), we will investigate the application of tDCS primarily targeting changes in emotion regulation abilities in children and adolescent with psychiatric disorders in general (transdiagnostic approach) as well as separately in each clinical disorder group (i.e., depressive, anxiety and conduct disorder subgroup). As secondary objective, we complementarily aim to investigate possible changes in disorder-specific clinical symptomatology (traditional, nosological approach; i.e., changes in the psychopathology of anxiety, depressive and conduct disorder). Thirdly, we will explore changes in quality of life, as well as in emotional and cognitive functioning in general.

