#### Secondary Hypotheses

We expect significant improvements in disorder-specific clinical symptomatology, quality of life, as well as in emotion recognition and regulation, attentional bias and working memory (in the related psychological, behavioral and physiological indices) in the experimental group, compared to the control group after the interventions.

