#### Sample Size Calculations

Given the planned study design with two treatment conditions (real and sham tDCS), two time points (before and after the intervention) and three diagnostic groups (anxiety, depressive and conduct disorder), a repeated-measures analysis of variance (rmANOVA) with the following parameters was set up: α = 0.0167 (0.05 corrected for three groups), power 1 – β = 0.80, a moderate effect size of f = 0.25 (73). The FEEL-KJ [German version of the Questionnaire for the assessment of emotion regulation in children and adolescents; (74)] as it is used for assessment of the primary endpoint was reported to have a test-retest reliability of r = 0.62, a Chronbach alpha of α = 0.93 for the adaptive strategy subscale and a Chronbach alpha of α = 0.82 for the maladaptive strategies, whereas for the 15 different emotion specific subscales Chronbach alphas between α = 0.69 – α = 0.91 were reported (74). Non-sphericity is of no relevance for only two repeated measures. This, results in a required sample size of 36 per group and 108 subjects overall.

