### Statistical Analysis

Regarding the primary endpoint, repeated-measures analysis of variance (rmANOVA) with Time (pre/post) and Treatment Condition (real stimulation/sham stimulation), as well as considering the three clinical subgroups will be conducted to investigate the interaction between times and groups on the dependent variable [FEEL-KJ raw scores (74)]. The sex and age of the participants will be used as blocking factor accounting for treatment variability between males and females and the three age groups, respectively. In the case of distributions not suitable for conventional testing and missing values, a generalized linear mixed model on the relationship between the stimulation condition and behavioral variables can be applied. Stimulation condition and time will be taken as the fixed-effect factors and the participant's ID as the random-effect factor. Parameters of the model will be fitted with the maximum-pseudolikelihood method, the appropriate distribution and link function according to the characteristics of the response data. A marginal ANOVA will follow to evaluate the fix-effect factors significance. The secondary endpoints, i.e., the indicators for aggression, depression, anxiety and quality of life, as well as cognitive and emotional functioning will be compared using the same approach. In order to identify the direction of effects, *post-hoc* tests will be employed.

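### The non-primary outcomes are given conflicting status (secondary hypotheses, secondary endpoints, exploratory), so the plan does not settle which of their p-values may support a claim

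*Protocol article*

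**What the plan says.** Four places in the protocol article assign a status to the outcomes other than the primary FEEL-KJ score.

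- **Introduction** (end of the part on tDCS in psychiatric disorders): "As secondary objective, we complementarily aim to investigate possible changes in disorder-specific clinical symptomatology". Quality of life and emotional and cognitive functioning follow as a third tier, to be explored.
- **Secondary Hypotheses**: "We expect significant improvements in disorder-specific clinical symptomatology, quality of life". The same sentence extends this expectation to emotion recognition and regulation, attentional bias and working memory, real versus sham.
- **Outcomes**: "As exploratory outcomes, we will investigate if the application of tDCS improves the disorder-related clinical symptomatology". Quality of life and emotion regulation are included, and the same sentence makes the corresponding self- and parent-rated raw scores secondary endpoints. The task indices are then only explored.
- **Statistical Analysis**: the secondary endpoints cover aggression, depression, anxiety and quality of life, "as well as cognitive and emotional functioning will be compared using the same approach" as the primary.

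The only significance level given is in Sample Size Calculations: "α = 0.0167 (0.05 corrected for three groups". A separate multiplicity correction is stated for the whole-brain fMRI analyses.

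**The concern.** The status of an outcome decides how its p-value may be read. An exploratory outcome needs no adjustment, but then the plan should not predict significance for it. An outcome that carries a hypothesis can support a claim, and then it matters how many such hypotheses there are and how error is controlled across them.

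Here one outcome can carry all the labels. Working memory is part of a hypothesis of significant improvement in one section, is explored in two others, and falls under the secondary endpoints in a fourth. With the results in hand, the text would support presenting a nominally significant score as a secondary hypothesis borne out, and a non-significant one as mere exploration. A reader of the final report could not use the protocol to tell the two apart.

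**Working it through.** **1. The plan's own figure, and what its alpha covers.** Inputs from Sample Size Calculations: "a moderate effect size of f = 0.25", "power 1 – β = 0.80", two arms, two time points, alpha 0.0167. I take the stated "test-retest reliability of r = 0.62" as the pre-post correlation; the text does not say that it was entered. For the time-by-arm interaction, the noncentrality is λ = f² × N × m / (1 − ρ). With N = 36 this gives 0.0625 × 36 × 2 / 0.38 = 11.8, and power 0.816. The smallest N that reaches 0.80 is 35, or 36 for equal arms, and 3 × 36 = 108. The stated size reproduces. The alpha is 0.05 / 3 = 0.0167, one third for each diagnostic group. It contains no allowance for the number of outcomes.

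**2. The labels side by side.**

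| Outcome | Introduction | Secondary Hypotheses | Outcomes | Statistical Analysis |
|---|---|---|---|---|
| Disorder-specific symptoms | secondary objective | significant improvement expected | exploratory and secondary endpoint | secondary, tested like the primary |
| Quality of life | third tier, explored | significant improvement expected | exploratory and secondary endpoint | secondary, tested like the primary |
| Cognitive and emotional functioning (tasks) | third tier, explored | significant improvement expected | explored | secondary, tested like the primary |

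No row keeps one status across the sections.

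**3. How many scores.** One score per form, from Psychological Self- and Parental Ratings, leaving out the primary and the diagnostic interview:
- emotion regulation (FEEL parent form, ERQ, ERC, ASQ-Y, DERS): 5
- YSR and CBCL: 2
- DISYPS-III, three scales by two informants: 6
- BDI, STAI, STAXI: 3
- empathy (IECA, ICU child, ICU parent, BES, GEM): 5
- KIDSCREEN, two informants: 2

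This makes 23 forms. The five computerised tasks at one index each bring it to 28. Secondary Hypotheses, Outcomes and Statistical Analysis do not name empathy; without those five scores the count is 28 − 5 = 23. Each task has several indices, so one per task is a low count.

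**4. Chance of at least one false significant improvement.** Assumptions: no true effect on any outcome, and two-sided tests at level α, of which only results favouring real stimulation count. The alpha for these outcomes is not stated, so 0.05 and 0.0167 are both shown.

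Independent tests: P = 1 − (1 − α/2)^m.
- m = 28, α = 0.05: 1 − 0.975^28 = 0.51, with 28 × 0.025 = 0.7 false improvements expected.
- m = 28, α = 0.0167: 1 − 0.99165^28 = 0.21.

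Correlated tests, with equal correlation r between test statistics: P = 1 − ∫ φ(u) Φ[(c − √r·u)/√(1 − r)]^m du, where c is the normal quantile at 1 − α/2. The values of r are assumptions.

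| m | α | independent | r = 0.3 | r = 0.5 | r = 0.7 |
|---|---|---|---|---|---|
| 28 | 0.05 | 51% | 34% | 25% | 17% |
| 28 | 0.0167 | 21% | 15% | 11% | 7% |
| 23 | 0.05 | 44% | 30% | 23% | 15% |

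For comparison, a single test at two-sided 0.05 has a 2.5% chance of a false improvement.

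**The case against.** The strongest reply is that adjustment across secondary endpoints is commonly left to the full protocol or the analysis plan, neither of which is shown, and that clearly labelled secondary or exploratory analyses need none. That stands: the lack of a stated adjustment is not a fault by itself. It does not answer the conflict of labels, because condensing a protocol into an article does not explain two statuses within one sentence.

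Several stronger readings are tempting, and the article does not support them.
- A reader might infer that these outcomes are declared confirmatory. That word is never used; the most the text offers is a hypothesis of significant improvement.
- A reader might infer that the plan has no error control beyond the primary. The whole-brain fMRI analyses have a stated correction, so the gap concerns questionnaires and tasks only.
- A reader might infer that a chance finding is close to certain. The figure 1 − 0.95^28 = 76% needs alpha 0.05, independence and differences in either direction. The hypothesis is about improvement, and self- and parent-ratings of the same construct are unlikely to be independent.
- A reader might multiply 28 by four, for the whole sample and three diagnoses, to reach 112 tests. Separate subgroup claims are stated for the primary only. Using the same approach for the secondaries may mean one model with diagnosis as a factor.

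The count is also soft, since it depends on the empathy scales and on one index per task.

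**Conclusion.** The point holds as an internal contradiction: the article gives the same outcomes incompatible status across the Introduction, Secondary Hypotheses, Outcomes and Statistical Analysis. It affects about 23 to 28 questionnaire and task scores, and the only stated alpha does not address their number.

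The consequence is moderate. With 28 null tests at 0.05, a false significant improvement somewhere has a probability of 51% under independence and about 17 to 34% at assumed correlations of 0.7 to 0.3. If 0.0167 carries over, the figures are 21% and about 7 to 15%. These rest on my count, on an alpha that the article does not state for these outcomes, and on assumed correlations. They do not show that a chance finding is likely on every reading. They show that it is common enough for the status of each outcome to need settling before the results are known. The primary analysis is not affected.

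**What to change.** Use one hierarchy, in the same words, in the Introduction, Secondary Hypotheses, Outcomes and Statistical Analysis. The Abstract, which groups all these outcomes as a second aim, should follow. There are two acceptable forms.

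1. Name a short set of secondary endpoints, chosen by the investigators, with the informant, the score, the alpha and the error control for each. One symptom score per diagnosis, with or without quality of life, under Holm at 0.05 would be one example; other sets and methods would serve. Everything else is exploratory.
2. Declare all non-primary outcomes exploratory.

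In either form, report each exploratory outcome as an estimate with a 95% confidence interval and make no claim of significance. Reword the Secondary Hypotheses so that significant improvement is expected only for named secondary endpoints, or for none.

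The cost is a revision of the text and a decision by the investigators on what to name. Named secondaries face a slightly stricter threshold, and the other outcomes lose claims of significance. No participants, visits or measurements are added.

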### Statistical Analysis

Regarding the primary endpoint, repeated-measures analysis of variance (rmANOVA) with Time (pre/post) and Treatment Condition (real stimulation/sham stimulation), as well as considering the three clinical subgroups will be conducted to investigate the interaction between times and groups on the dependent variable [FEEL-KJ raw scores (74)]. The sex and age of the participants will be used as blocking factor accounting for treatment variability between males and females and the three age groups, respectively. In the case of distributions not suitable for conventional testing and missing values, a generalized linear mixed model on the relationship between the stimulation condition and behavioral variables can be applied. Stimulation condition and time will be taken as the fixed-effect factors and the participant's ID as the random-effect factor. Parameters of the model will be fitted with the maximum-pseudolikelihood method, the appropriate distribution and link function according to the characteristics of the response data. A marginal ANOVA will follow to evaluate the fix-effect factors significance. The secondary endpoints, i.e., the indicators for aggression, depression, anxiety and quality of life, as well as cognitive and emotional functioning will be compared using the same approach. In order to identify the direction of effects, *post-hoc* tests will be employed.

Single-subject analysis of the fMRI data will be conducted using the general linear model (GLM) as implemented in SPM12. The conditions will be modeled as previously described for the eSTROOP (120), e-nBACK (124) and the ERT [similar to (123)]. Image-derived movement estimates and surrogates of physiological artifacts (heartbeat, breathing) will be used as covariates and regressed out. The same corrections will be applied to the RS data, which will be used for estimating functional connectivity using in-house software. Group analyses of the whole-brain fMRI data will be again conducted using the GLM in SPM12. The Sandwich Estimator (SwE) will additionally be utilized for missing data. Diagnostic group and measurement (pre-/post-intervention) will be used as model factors. Subject age and sex will further be corrected for on group-level. Besides factorial group analysis, exploratory correlations will be calculated with indicators of disorder-specific impairments and emotion regulation capabilities. For multiplicity correction, SPM12 uses random field theory based on the smoothness of the data and SwE a bootstrapping approach.

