### Hypotheses

#### Primary Hypothesis

We expect that the participants of the experimental group (in total i.e., transdiagnostic, as well as in each clinical subgroup) will significantly improve in emotion regulation after real tDCS, when compared to the control group (in total i.e., transdiagnostic, as well as in each clinical subgroup) after receiving sham stimulation.

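### The primary hypothesis claims an effect in each of three diagnoses, but no stated analysis clearly tests whether that effect is shared or differs, and the fallback mixed model as written cannot

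*Protocol article*

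**What the plan says.** All places are in the protocol article.

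- **Aim** (end of the Introduction, in the section on tDCS in psychiatric disorders): emotion regulation is to be studied in psychiatric disorders in general, which the article calls the transdiagnostic approach, "as well as separately in each clinical disorder group".
- **Primary Hypothesis:** the real-versus-sham difference is expected "in total i.e., transdiagnostic, as well as in each clinical subgroup". Outcomes repeats this for the FEEL-KJ raw score.
- **Sample Size Calculations:** two treatment conditions, two time points and three diagnostic groups are listed, and "a repeated-measures analysis of variance (rmANOVA) with the following parameters was set up": "α = 0.0167 (0.05 corrected for three groups"), "power 1 – β = 0.80" and "a moderate effect size of f = 0.25". A "test-retest reliability of r = 0.62" is reported for the FEEL-KJ. The result is 36 per group and 108 overall.
- **Stratification and Randomization:** allocation is 1:1 within each diagnosis, 18 real and 18 sham.
- **Statistical Analysis:** an rmANOVA with Time and Treatment Condition, "as well as considering the three clinical subgroups will be conducted to investigate the interaction between times and groups". If distributions are unsuitable or values are missing, a generalized linear mixed model may be used instead. Its fixed effects are stimulation condition and time, with participant as the random effect. Diagnosis is not among them.

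**The concern.** The hypothesis makes one pooled claim and three diagnosis-level claims, and the trial is sized for the latter. Three separate significance verdicts do not show whether the effect is the same or different across diagnoses, because a difference in significance is not evidence of a difference in effect. That comparison needs the Time x Treatment x Diagnosis interaction, which the article does not name.

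This matters because the rationale is a shared deficit with a shared neural basis. If one or two diagnoses reach significance and the rest do not, a reader will want to know whether the effect is disorder-specific. Under the stated plan that question may have no valid test behind it, and under the fallback model it has none.

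**Working it through.** **Inputs.** From Sample Size Calculations: alpha = 0.0167, target power 0.80, f = 0.25, reliability 0.62, 36 per diagnosis. From Stratification and Randomization: 18 versus 18 per diagnosis. Assumed: the reliability of 0.62 serves as the pre-post correlation r (the article does not say so), the diagnoses are independent, there is no dropout, and sex and age blocking is ignored.

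**1. Reproduce the sample size.** For a Time x Treatment interaction with two arms and two times, the noncentrality is lambda = f² x N x 2 / (1 - r), with 1 and N - 2 df.

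- N = 36, r = 0.62: lambda = 0.0625 x 36 x 2 / 0.38 = 11.84, power 0.816. This is the smallest even N that reaches 0.80, and 3 x 36 = 108.
- Alternatives do not match. r = 0.5 needs 46. Alpha 0.05 needs 26 (r = 0.62) or 34 (r = 0.5). Interactions of time with three or six groups, at alpha 0.0167 and r = 0.62, need 45 or 60 in total.

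So the stated size is that of one separate 2 x 2 test inside each diagnosis. The exact match also supports reading 0.62 as the correlation.

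**2. Three tests when the effect is equal.** With power p per diagnosis, all three are significant with probability p³ and none with (1 - p)³. The mixed pattern (one or two significant) has probability 1 - p³ - (1 - p)³.

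| Effect | r | p | All three | None | Mixed |
|---|---|---|---|---|---|
| f = 0.25 (planned) | 0.62 | 0.816 | 0.54 | 0.006 | 0.45 |
| f = 0.25 (planned) | 0.5 | 0.684 | 0.32 | 0.03 | 0.65 |
| f = 0.20 | 0.62 | 0.596 | 0.21 | 0.07 | 0.72 |
| f = 0.125 (half) | 0.62 | 0.228 | 0.01 | 0.46 | 0.53 |

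For the first row: 1 - 0.816³ - 0.184³ = 0.450. A simulation of 100,000 trials also gave 0.450 there, and 0.647 for the second row. The last two rows use effects that are not in the plan and serve only to show the range.

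**3. The pooled test.** With N = 108, alpha 0.05 and r = 0.62, lambda = 0.0625 x 108 x 2 / 0.38 = 35.5 and power exceeds 0.99. At f = 0.15 it is 0.94.

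**4. The three-way test.** In SD units of the change score, the planned effect is d = sqrt(8 x 0.0625 / 0.38) = 1.147 at r = 0.62, and 1.0 at r = 0.5. With 18 per arm, lambda = 9 x the sum of squared deviations of the three effects from their mean, on 2 and 102 df. For effects (d, d, 0) the sum is (2/3)d², so lambda = 9 x 0.667 x 1.316 = 7.89. Power at alpha 0.05:

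| Effects | r = 0.62 | r = 0.5 |
|---|---|---|
| d, d, 0 or d, 0, 0 | 0.70 | 0.57 |
| d, d/2, 0 | 0.57 | 0.45 |
| d, d/2, d/2 | 0.22 | 0.17 |

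With equal effects at r = 0.62, the simulated test rejects in 5% of all trials and in 9.6% of those showing a mixed pattern. It therefore lends no support to disorder specificity in about 90% of the trials where the separate verdicts might suggest it.

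**5. What a joint model does to mixed patterns.** With error pooled over the six cells (102 df), power per diagnosis rises from 0.816 to 0.841. Treating the three tests as independent, the mixed pattern has probability 1 - 0.841³ - 0.159³ = 0.40.

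**The case against.** The strongest reply is that the rmANOVA may already contain the term. Statistical Analysis mentions the three subgroups alongside the two named factors, and Sample Size Calculations describes a layout of two treatments, two times and three diagnoses. A full factorial analysis of that layout includes the three-way interaction. Sizing on the smallest contrast is compatible with analysing everything in one model, and an article need not list every term. This stands in part: a reader might infer that diagnosis is left out of the rmANOVA, but the text is ambiguous and does not establish that. It does not rescue the fallback, whose fixed effects are listed without diagnosis. Fitted to all participants, that model gives neither diagnosis-specific effects nor a test of their difference. Fitted separately by diagnosis, it gives the former but not the latter. Missing values are one of its stated triggers, so its use is a realistic prospect.

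A reader might also infer that the transdiagnostic question goes unanswered. It does not. The article defines that approach as the effect in psychiatric disorders in general, makes the pooled comparison part of the primary hypothesis, and has ample power for it.

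Nor does the article say that a mix of significant and non-significant diagnoses will be read as disorder specificity. That misreading is a risk left open, not a stated rule. Finally, the joint model barely lowers the chance of a mixed pattern (45% to about 40%), and its interaction test cannot prove that effects are equal. Both points are correct.

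**Conclusion.** The concern holds in a limited form. The article claims effects in each diagnosis and sizes the trial on three separate within-diagnosis tests, yet no stated analysis clearly tests whether the effect differs between diagnoses. The rmANOVA wording leaves this open, and the fallback as written cannot do it. At the planned effect, equal in all three diagnoses, a mixed pattern arises in about 45% of trials with r = 0.62 and 65% with r = 0.5. These figures rest on the assumptions listed with the calculation, chiefly r. They measure how often the question of interpretation would arise, not how often it would be answered wrongly. The point is worth correcting, but it does not undermine the pooled primary comparison.

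**What to change.** In Statistical Analysis, state for both the rmANOVA and the fallback mixed model that all 108 participants are fitted with Time, Treatment, Diagnosis and their interactions. Diagnosis already structures the randomisation. From this joint model, report the pooled Time x Treatment effect and the three diagnosis-specific effects, each with a confidence interval. State that any claim of differing effects rests on Time x Treatment x Diagnosis, and not on some diagnoses being significant and others not.

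The cost is wording only; sample size and data collection are unchanged. The downside is the moderate power of the interaction test shown above, so a non-significant result must be read with the confidence intervals and does not show equal effects. Mixed patterns will still occur; the joint model gives a valid basis for interpreting them.

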#### Stratification and Randomization

In a first step, participants displaying T-values of the FEEL-KJ Total score outside the clinical norm (T-value <40 or >60 in accordance with the transdiagnostic inclusion criterion of substantial emotion dysregulation) and in addition fulfilling the primary diagnosis of either a depressive, anxiety or conduct disorder, will be included in the study. Secondary diagnosis, especially comorbid disorders related to another subgroup of the current trial (e.g., primary diagnosis: depression and secondary diagnosis: anxiety) will be recorded and taken into consideration for the analysis. Age and sex will serve as stratification variables allocating 12 participants of each clinical group to one age block (age block1: 13 + 14 years; age block 2: 15 + 16 years; age block 3: 17 + 18 years) with half of the participants per age block being female and the other half male.

In a second step, a block randomization is performed: 50% of the participants of each block of each subgroup will be randomly allocated to the real or sham tDCS group, respectively (18 of 36 for each of the three clinical groups, female: male = 1:1). This results in 54 subjects per experimental condition (balanced related to clinical groups, age and sex; see Figure 1).

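### The primary time-by-treatment test is valid but equals a change-score test; adjusting for the baseline FEEL-KJ already collected would be more precise

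*Protocol article*

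**What the plan says.** Under Outcomes, the endpoint is defined as change: "The primary outcome of this study is the change in emotion regulation ability, measured by the raw score of the FEEL-KJ". Under Statistical Analysis, the test is a repeated-measures ANOVA with time (pre, post) and treatment condition, taking the three diagnostic groups into account, "to investigate the interaction between times and groups on the dependent variable". Sex and age are the only blocking factors named. The mixed model held in reserve for awkward distributions or missing values has condition and time as fixed effects and participant as random effect. Neither model has baseline FEEL-KJ as a covariate. The secondary endpoints follow the same approach.

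Sample Size Calculations sets "α = 0.0167 (0.05 corrected for three groups") and "power 1 – β = 0.80, a moderate effect size of f = 0.25", says that the FEEL-KJ "was reported to have a test-retest reliability of r = 0.62", and concludes that this "results in a required sample size of 36 per group and 108 subjects overall". Stratification and Randomization allocates "18 of 36 for each of the three clinical groups" to each condition. Procedure and Intervention places the questionnaires before stimulation, so a baseline value is collected for every participant who starts treatment.

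**The concern.** With one pre and one post measurement, the time-by-treatment F statistic is the square of the t statistic on change scores. That test in effect subtracts the whole baseline from the post score, which fixes the baseline slope at 1. With a correlation of 0.62 and similar pre and post SDs the slope is about 0.62, so the change score carries avoidable baseline noise. In a randomised trial, adjusting for baseline estimates the same treatment effect with a smaller residual variance, and also corrects for chance baseline differences.

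Precision is at stake, and mainly within diagnosis. The Primary Hypothesis claims an effect in each clinical subgroup, with 18 per arm. The stated size only just reaches 80% power there, and the sample-size section shows no allowance for dropout.

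**Working it through.** **Inputs.** Alpha 0.05/3 = 0.0167, power 0.80, f = 0.25 and r = 0.62 (Sample Size Calculations); 18 per arm in each diagnosis and 54 per arm overall (Stratification and Randomization). SDs are taken as equal before and after, and variances are in units of SD². Age and sex are left out of both calculations.

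**1. The plan's own figure.** In a 2 x 2 design, f = 0.25 for the interaction puts ±0.25 SD in each cell, so the arms differ in change by 4 × 0.25 = 1.0 SD. The noncentrality is λ = f² × N × m/(1 − r) = 0.0625 × 36 × 2/0.38 = 11.84, with 1 and 34 df. Power is 0.816. The minimum N is 35, or 36 with equal arms, and 3 × 36 = 108. The stated size is reproduced, and r = 0.62 is the value that reproduces it; r = 0.5 would give 46 per diagnosis.

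**2. The same test as a t-test on change.** The change variance is 2(1 − 0.62) = 0.76. The standard error at 18 per arm is √(0.76 × 2/18) = 0.2906. Then 1.0/0.2906 = 3.441, and 3.441² = 11.84, as in step 1.

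**3. Baseline-adjusted.** The residual variance is 1 − 0.62² = 0.6156. The ratio to change is 0.6156/0.76 = (1 + 0.62)/2 = 0.81, which is 19% lower.

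**4. Price of adjustment.** One df is lost, and chance imbalance inflates the variance by about 1 + 1/(N − 4): 1.031 at N = 36 and 1.010 at N = 108. The net ratios are 0.81 × 1.031 = 0.835 and 0.81 × 1.010 = 0.818.

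**5. Power at r = 0.62.**

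| Comparison | Difference | Alpha | Change score | Adjusted |
|---|---|---|---|---|
| 18 v 18 | 1.0 SD (planning effect) | 0.0167 | 0.816 | 0.896 before, about 0.886 after imbalance |
| 54 v 54 | 0.5 SD (assumed) | 0.05 | 0.84 | 0.907 before, about 0.90 after imbalance |
| 54 v 54 | 1.0 SD (planning effect) | 0.05 or 0.0167 | above 0.999 | above 0.999 |

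Simulation of the 18 v 18 case gave 0.819 and 0.886. For 80% power within a diagnosis, 30 patients would do instead of 36.

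**6. Other correlations.** The ratio (1 + r)/2 before the imbalance cost is 0.70 at r = 0.4, 0.75 at 0.5, 0.85 at 0.7, 0.90 at 0.8 and 0.95 at 0.9.

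**7. Selected entry.** Inclusion requires T < 40 or T > 60. Suppose the screening score is also the baseline, scores are bivariate normal and r = 0.62 in the unselected population. The slope stays at 0.62 and the adjusted variance at 0.6156, while the change variance is (1 − 0.62)² × (baseline variance) + 0.6156.
- Only T < 40 enters: baseline variance 0.199; change variance 0.1444 × 0.199 + 0.6156 = 0.644; ratio 0.955.
- Both tails enter: baseline variance 2.525; change variance 0.1444 × 2.525 + 0.6156 = 0.980; ratio 0.628.

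The gain is therefore about 4% to 37% before the imbalance cost. In the one-tail case the net ratio is about 0.985 at N = 36 and 0.965 at N = 108, a gain of 1.5% to 3.5%.

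**The case against.** The strongest objection is that nothing here is wrong. The repeated-measures ANOVA is unbiased under randomisation, matches an endpoint defined as change, and is the test for which the trial was sized. It reaches the stated power. All of that stands. A reader might infer that the primary analysis is biased or that 108 is miscalculated; the documents support neither.

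Four further limits also stand.
- The figure of 0.62 is reported as a property of the questionnaire, not as the correlation expected in this sample. Under one-tail entry the gain is close to nothing.
- A reader might argue that selecting patients with extreme scores pushes the slope below 1. It does not: under linear bivariate normality, selection on baseline leaves the slope at 0.62 and moves only the in-sample correlation (0.33 with one tail, 0.78 with both). The slope is below 1 because retest agreement is imperfect.
- A reader might take the pooled comparison to be short of power. The rise from 0.84 to about 0.90 needs a 0.5 SD effect, which the protocol does not state.
- A gain of 19% on every questionnaire cannot be claimed, because a test-retest figure is given for the FEEL-KJ only.

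Two objections do not hold. The choice of primary model is not a detail left to an unseen analysis plan, since the article names both the model and its factors. Pre-measures are taken after randomisation, but before stimulation and under blinding, so they can serve as a covariate.

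**Conclusion.** The point holds as a matter of efficiency, and the change is worth making. At r = 0.62, assumed to apply to this sample, the variance of the treatment estimate falls by about 19%, or about 16% net within a diagnosis, and subgroup power at the planning effect rises from 0.82 to about 0.89. The direction is secure: none of the correlations and entry patterns examined gives a loss. The size is not secure. If the screening score is the baseline, it runs from about 4% to 37% before the imbalance cost, depending on which tails enrol; if the FEEL-KJ is measured afresh after inclusion, that range does not apply as it stands. The benefit falls on the three subgroup comparisons; at the planning effect the pooled test gains nothing material.

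**What to change.** Analyse the post-intervention FEEL-KJ raw score in a linear model with treatment, diagnostic group, age block, sex and the baseline FEEL-KJ raw score. Include treatment-by-diagnosis contrasts, because each subgroup is part of the primary hypothesis. Using change as the response with the same covariates gives the identical treatment estimate, so the endpoint definition can stay. State which FEEL-KJ administration is the baseline. If both tails are enrolled, check that one straight baseline slope fits across them. Say how the reserve mixed model for missing values relates to this model, so that the adjustment is not lost there.

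Add each secondary questionnaire's own baseline in the same way, without claiming a particular gain. Keep the repeated-measures ANOVA as a sensitivity analysis, and fix the change before unblinding.

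The statistical cost is one degree of freedom and an imbalance factor of about 3% at N = 36 and 1% at N = 108. No new visits, data or patients are needed. The sample size can stand; its section needs a sentence saying that it was calculated for the unadjusted test.
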